## Abstract

**Background:**

Dengue is the most important vector-borne viral infection of man, with approximately 2 billion people living in areas at risk. Infection results in a range of manifestations from asymptomatic infection through to life-threatening shock and haemorrhage. One of the hallmarks of severe dengue is vascular endothelial disruption. There is currently no specific therapy and clinical management is limited to supportive care. Statins are a class of drug initially developed for lipid lowering. There has been considerable recent interest in their effects beyond lipid lowering. These include anti-inflammatory effects at the endothelium. In addition, it is possible that lovastatin may have an anti-viral effect against dengue. Observational data suggest that the use of statins may improve outcomes for such conditions as sepsis and pneumonia. This paper describes the protocol for a randomised controlled trial investigating a short course of lovastatin therapy in adult patients with dengue.

**Methods/design:**

A randomised, double-blind, placebo-controlled trial will investigate the effects of lovastatin therapy in the treatment of dengue. The trial will be conducted in two phases with an escalation of dose between phases if an interim safety review is satisfactory. This is an exploratory study focusing on safety and there are no data on which to base a sample size calculation. A target sample size of 300 patients in the second phase, enrolled over two dengue seasons, was chosen based on clinical judgement and feasibility considerations. In a previous randomised trial in dengue, about 10% and 30% of patients experienced at least one serious adverse event or adverse event, respectively. With 300 patients, we will have 80% power to detect an increase of 12% (from 10% to 22%) or 16% (from 30% to 46%) in the frequency of adverse events. Furthermore, this sample size ensures some power to explore the efficacy of statins.

**Discussion:**

The development of a dengue therapeutic that can attenuate disease would be an enormous advance in global health. The favourable effects of statins on the endothelium, their good safety profile and their low cost make lovastatin an attractive therapeutic candidate.

**Trial registration:**

International Standard Randomised Controlled Trial Number ISRCTN03147572

## Background

Dengue is the most common and important vector-borne viral infection of man, with at least 2 billion people living in areas of risk [1]. Clinical dengue varies from asymptomatic infection to severe disease characterised by shock and haemorrhage. There are currently no specific therapeutic agents and disease management is limited to careful fluid management [2,3].

### Statins

Statins are inhibitors of 3-hydroxy-3-methylglutaryl-coenzyme A (HMG-CoA) reductase. They were first used clinically in the late 1980s and quickly became established as an effective drug for both lipid lowering and mortality reduction in cardiovascular disease [4]. They are currently one of the most prescribed classes of drugs globally. Statins have an excellent safety profile [5]. The most common adverse effects are rises in the level of liver transaminases and myopathy. These effects are rare and appear to be dose-related [5,6]. More recent research has demonstrated that statins have additional beneficial effects. These pleiotropic effects include the restoration or improvement of endothelial cell function, an increased production of nitric oxide, and a reduction in the release of cytokines and acute phase proteins. These effects lead to a reduction of inflammation within the vessel wall [7,8]. Observational studies suggest that statin therapy may result in improved outcomes for a diverse range of conditions, including sepsis and pneumonia [9-13]. In addition, there are a number of on-going randomised clinical trials to assess the therapeutic efficacy of statins in sepsis and acute lung injury (NCT00528580, NCT00676897, NCT00979121).

### Statins and dengue

One of the major features of both dengue and sepsis is widespread vascular endothelial disruption resulting, in part, from exposure to inflammatory mediators [14-16]. This suggests that in view of their pleiotropic effects, it is plausible that statins may favourably augment the pathophysiological mechanisms of these two conditions. A study in healthy volunteers showed that the endotoxin-induced inflammatory response was suppressed in those receiving a statin at a high dose (simvastatin 80 mg), perhaps explaining the beneficial effect observed in sepsis [8,17]. Furthermore, *in vitro* work has demonstrated that lovastatin may have an anti-viral effect in dengue by reducing virion assembly [18,19].

### Choice of study drug

We have chosen lovastatin as the study drug for both scientific and pragmatic reasons. In light of the US Food and Drug Administration’s safety recommendations about the risks of muscle toxicity with simvastatin, there were concerns from the regulatory authorities in Vietnam about the safety of using this agent in dengue. An additional reason for our choice was the dengue anti-viral effect observed with lovastatin in *in vitro* experiments [18]. As this effect may also be observed *in vitro*, we believe it is rational to test the drug used in the original work. Furthermore, lovastatin is commonly prescribed and available in Vietnam as a generic and will therefore be immediately available to patients if there is a positive result from the trial.

### Aims of the trial

Typically, severe vascular leakage and shock occur around the fifth day of illness in patients with dengue [20]. It is possible that initiation of statin therapy early in the course of the illness may prevent or favourably modulate these effects. As the proportion of patients who develop shock or other complications after presentation to hospital is low (approximately 5%), a large trial would be required to demonstrate a clinical benefit [2,21]. However, this study presents an opportunity to assess formally the safety of using statins in the treatment of this disease. In addition, such a study will also provide an opportunity to investigate the effect of statin usage on the immune response during dengue infection and to generate preliminary data for planning a Phase III trial in the future.

Although there is extensive experience of using statins as a lipid-lowering agent, and an increase in the amount of observational data from their use in critically ill patients, this will be the first study looking at the use of statins in dengue. We propose to investigate the effect of lovastatin for 5 days in adult dengue patients presenting in the first 72 hours of illness. The rational of a 5-day treatment course is to cover the transient ‘critical’ phase of infection when complications arise, which typically occurs around the fifth day of illness [3]. Our proposed treatment course will start on the second or third day of illness and continue to the seventh or eighth day of illness, which is into the recovery phase. As this is the first study investigating statin therapy in dengue with a particular focus on safety, we propose a dose-escalation study, investigating 40 mg lovastatin versus placebo with a safety review after recruitment of the first 30 patients. If this review is satisfactory, we will increase the lovastatin dose to 80 mg and conduct a further safety review after the next 30 patients.

## Methods/design

### Design

This study is a randomised, placebo-controlled, double-blind trial investigating lovastatin therapy in Vietnamese adults with dengue infection. The trial will be conducted in two phases, with an escalation of dose between phases if the results of an interim data review show no safety concerns within the first cohort of patients treated with the lower dose.

Patients will be followed for clinical and laboratory endpoints in hospital until study day 6 (or daily as out-patients from discharge to day 6) and reviewed at an outpatient visit on day 28.

### Inclusion and exclusion criteria

All patients aged 18 or more presenting to the Hospital of Tropical Diseases, Ho Chi Minh City with a clinical suspicion of dengue, less than 72 hours of fever and a positive rapid test for dengue non-structural protein 1 (NS1) will be eligible for recruitment into the study. Exclusion criteria are: signs or symptoms suggestive of another acute infectious disease, alanine transaminase levels greater than 150 U/l, creatine kinase levels greater than 1000 U/l, liver cirrhosis, myopathy, current or use within past week of statins, pregnancy and lactation. In addition, patients taking medications contraindicated for use with statins, for example, isoniazid for treatment of tuberculosis, will be excluded.

### Primary endpoint

The primary endpoint of this study is an evaluation of the safety and tolerability of lovastatin therapy in adult patients with dengue. Comparing the rates of adverse events between randomised treatment arms will assess this.

### Secondary endpoints

The secondary endpoints of this study are fever clearance time (see definition), plasma viraemia (area under the log-transformed viraemia curve from enrolment until study day 6), platelet nadir between day 3 and 8 of illness, maximum haematocrit between day 3 and 8 of illness, percentage increase in haematocrit between day 3 and 8 of illness from baseline, maximum alanine transaminase (ALT) and creatine kinase (CK) recorded between day 3 and 8 of illness, lowest oxygen saturation recorded between day 3 and 8 of illness, number of patients in each group requiring colloid, and disease progression as defined by one or more of the following: (a) admission to the ICU, (b) diagnosis of shock (see definition), (c) diagnosis of severe bleeding (see definition), (d) development of encephalitis, (e) death. In addition, quality of life scores obtained using a visual analogue scale will be compared between treatment groups. The times from enrolment to the first sample with viraemia less than 1000 copies/ml and the first negative NS1 antigenaemia sample will be compared between treatment groups.

### Definitions

1. Fever clearance time is the time from enrolment to the first time the temperature falls to <37.5°C and remains below this level for 48 hours.

2. Shock: cardiovascular decompensation requiring fluid resuscitation and considered to be due to plasma leakage.

3. Severe bleeding is clinically severe if it results in haemodynamic instability or requires fluid resuscitation or a blood transfusion. Any bleeding resulting in death and any intracranial bleed are considered severe.

4. Baseline haematocrit: the haematocrit value obtained at the day 28 follow-up visit, or (if the day 28 value is missing) the expected age- and sex-matched population value.

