#### Laboratory evaluation

Haematocrit, platelet and total cholesterol measurements will be carried out daily or more frequently if clinically indicated. These tests will be repeated at the follow-up visit.

Renal and liver function tests, electrolytes and coagulation profiles, will be carried out at enrolment, 48 hours later, day 5 or 6 of illness and at the follow-up visit. If the ALT measured 48 hours after enrolment is greater than 250 U/l, the study drug will be discontinued. It should, however, be noted that hepatic dysfunction might be secondary to dengue infection and could be positively affected by statin therapy.

Conventional serological and virological tests will be used to confirm dengue infection and identify the infecting serotype. Plasma samples collected at daily intervals until discharge (and daily until day 6 if discharged before day 6) will be assessed for viraemia levels, NS1 levels, and concentrations of various pro- and anti-inflammatory cytokines (TNF-α, IFN-γ, IL-6, IL-10).

DNA will be extracted from residual blood samples and genotyped for genetic variants known to be associated with severe dengue, for example, *MICB* and *PLCE1*[22].

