#### Statistical analysis

The primary analysis population will include all patients randomised to placebo from cohort 1 and all patients (regardless of treatment assignment) from cohort 2 according to the intention-to-treat principle. Owing to their low number, patients randomised to low-dose statins from cohort 1 will only be descriptively analysed.

The proportion of patients with any adverse events, any serious adverse events, or specific adverse events will be summarised and compared between the treatment arms based on Fisher’s exact test.

Pre-defined secondary endpoints will be compared between the two treatment arms based on linear regression for continuous endpoints, logistic regression for binary endpoints, and Cox regression for time-to-event endpoints. For laboratory markers, comparisons will be adjusted for the pre-dose value of the respective marker and the day of illness at enrolment; plasma viraemia and NS1-endpoints will additionally be adjusted for dengue serotype.

The clinical, virological and immunological findings will also be correlated with *MICB* and *PLCE1* genotype using descriptive statistical methods.

A detailed statistical analysis plan will be finalised prior to unblinding the study data base.

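### When the day 28 haematocrit is missing, the population fallback adds the patient's own deviation from the norm to the percentage rise: mainly avoidable noise in one secondary endpoint

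*Protocol article*

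**What the plan says.** Under Secondary endpoints, the protocol article lists "percentage increase in haematocrit between day 3 and 8 of illness from baseline" and, separately, "maximum haematocrit between day 3 and 8 of illness". Only the first needs a baseline.

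Definition 4 supplies that baseline in two steps. The main rule is "Baseline haematocrit: the haematocrit value obtained at the day 28 follow-up visit". The fallback is "if the day 28 value is missing) the expected age- and sex-matched population value".

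Other sections show what else is known about each patient:

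- Laboratory evaluation: "Haematocrit, platelet and total cholesterol measurements will be carried out daily or more frequently if clinically indicated".
- Inclusion and exclusion criteria: fever must have lasted under 72 hours at entry.
- Aims of the trial: "severe vascular leakage and shock occur around the fifth day of illness in patients with dengue".
- Statistical analysis: continuous endpoints are compared by linear regression, and for laboratory markers "comparisons will be adjusted for the pre-dose value of the respective marker and the day of illness at enrolment".

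The article gives no haematocrit SD, no SD of the rise and no expected share of missing day 28 values.

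**The concern.** The fallback puts two different quantities into one variable. For a patient who returns on day 28, the endpoint is a within-person rise. For one who does not, it is the peak relative to an average person of the same age and sex. The second equals the first only when the patient's normal level happens to match the norm.

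The rule also passes over better information. Patients enrol early and severe leakage typically comes around day 5, so the pre-dose haematocrit usually precedes the main leakage phase and carries information about that person's normal level. The fallback does not use it.

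At stake is the precision of one secondary endpoint, the only listed one that expresses haemoconcentration relative to baseline.

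**Working it through.** The article states no figure for this endpoint, so there is none to reproduce. Every numerical input below is an assumption unless a section is named.

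**1. Algebra (no assumption needed).** Let B be the patient's own normal haematocrit, M the population value and R the true rise. Peak = B(1+R).

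- Own baseline: B(1+R)/B − 1 = R.
- Population baseline: (1+R)B/M − 1.
- Error from the fallback: (1+R)(B − M)/M.

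**2. Single patients, M = 42.**

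| True rise | Own normal | Scored rise |
|---|---|---|
| 15% | 37 | 37 × 1.15/42 − 1 = 1.3% |
| 15% | 39 | 39 × 1.15/42 − 1 = 6.8% |
| 15% | 45 | 45 × 1.15/42 − 1 = 23.2% |
| 10% | 38 | 38 × 1.10/42 − 1 = −0.5% |
| 10% | 46 | 46 × 1.10/42 − 1 = 20.5% |

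A deviation of 3 to 5 points moves the score by about 8 to 14 percentage points, which is comparable with the rise itself.

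**3. Error SD per fallback patient.** With a mean rise of 12%, it is about 1.12 × SD(B)/42:

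- SD 2.5: 1.12 × 2.5/42 = 6.7 percentage points.
- SD 3.0: 1.12 × 3.0/42 = 8.0.
- SD 3.5: 1.12 × 3.5/42 = 9.3.

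If the baseline is instead predicted from the patient's own pre-dose value (measurement error SD 1, pre-dose value already carrying 20% of the rise), the error SD is 2.7 to 2.8.

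**4. How much of the variation among fallback patients is deviation.** Inputs: M = 42, SD(B) 2 to 4 points, mean rise 10%, rise SD 5 to 15 percentage points, within-person error SD 1, pre-dose value carrying 20% of the rise.

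- Unadjusted share of variance: 0.11 to 0.78, and 0.37 in the middle case (SD 3, rise SD 10).
- After the pre-dose adjustment planned under Statistical analysis, fitted to the whole sample with 5 to 20% missing: 0.00 to 0.76, and 0.17 to 0.23 in the middle case.

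The adjustment helps, but not reliably, because one common slope has to serve two kinds of baseline.

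**5. Effect on the treatment comparison.** Simulated trials of 300 patients, 1:1, mean rise 12%, analysed by linear regression on arm and pre-dose haematocrit, with missingness unrelated to arm or outcome. Entries are the increase in treatment-effect variance under the stated fallback, relative to a baseline predicted from the own pre-dose value. Each range runs over person-to-person SD 2.5 to 3.5.

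| Day 28 missing | Rise SD 6 | Rise SD 10 | Overall, taking in repeat runs |
|---|---|---|---|
| 5% | 3-8% | 1-4% | 1-9% |
| 10% | 5-17% | 2-7% | 2-17% |
| 20% | 10-26% | 5-10% | 5-26% |

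Repeat runs move single entries by one to three percentage points. Mean treatment effects stayed near zero when none was simulated, so no bias appeared.

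On the standard-error scale the overall ranges are smaller: √1.01 to √1.09 is 0.5-4.4%, √1.02 to √1.17 is 1.0-8.2%, and √1.05 to √1.26 is 2.5-12.2%.

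**The case against.** The stated rule can be defended. It is simple, fixed in advance, blind to arm and independent of values taken during acute illness. Febrile-phase haematocrit can be shifted by dehydration, fluids or early leakage, so the pre-dose value is not a clean normal level. That point stands against using the pre-dose value directly as the baseline. It does not stand against a prediction model fitted in patients who have both values, because such a model calibrates out a systematic shift.

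The planned adjustment already brings the patient's own pre-dose value into the analysis. This stands in part: it lowers the noise but does not remove it.

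Missing-data methods are often left to the analysis plan, which is not shown. Here, however, the article has itself fixed the fallback, and the comment is on that stated rule.

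A reader might infer two stronger things:

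- **That the endpoint then mostly measures deviation from average.** This needs SDs that the article does not give. Over the range examined, the deviation is more often a minority of the variance than a majority. It passes half only when normal levels vary widely relative to true rises.
- **That the treatment comparison is biased.** Allocation is randomised and blinded, all patients are asked to attend on day 28, and nothing in the article links attendance to arm or severity. Patients who die before day 28 necessarily receive the population value, so some outcome-related missingness is possible, but the article gives no basis for sizing it. Even severity-related missingness would bias the comparison only if it differed by arm or interacted with treatment.

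**Conclusion.** The point holds as a modest loss of precision. Definition 4 mixes a within-person rise with a peak relative to an average person, and it does so although the patient's own earlier haematocrits are available. The cost is the variance inflation in the overall column of the table. It is near the lower end if attendance is high or true rises vary widely, and near the upper end if 20% are missing and rises vary little. The direction follows from algebra; the size rests on the assumed SDs and missing rates.

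It would be wrong to conclude that the haematocrit results as a whole are compromised. Maximum haematocrit needs no baseline and is untouched, the primary safety endpoint is not involved, and patients with a day 28 value are scored as intended. This is a cheap improvement to a stated rule, not a threat to the trial's conclusions.

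**What to change.** Amend the fallback in definition 4. When the day 28 value is missing, predict the baseline, preferably by multiple imputation, from the patient's own pre-dose haematocrit, day of illness at enrolment, age and sex. Fit the model in patients who have a day 28 value, so that any systematic acute-phase shift is calibrated out. Leave study day 6 values out of the predictors, since they can fall inside the day 3 to 8 illness window that defines the peak. Keep the population value as a sensitivity analysis, and report the number of patients by arm whose baseline was not observed.

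No new data are needed. The change fits the detailed analysis plan that the article says will be finalised before unblinding. The downside is that the fallback becomes model-based instead of a fixed table value, with a little extra analysis work.

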### Randomization procedure

Randomization to either treatment arm will be in a 1:1 ratio. Randomization will be stratified according to the ward of recruitment. A randomization list will be prepared and maintained confidentially from study staff by the clinical trials pharmacist. Block randomization using variable block sizes will be used.

A chronological log of all enrolled patients will be maintained. Each enrolled patient will be assigned the next available sequential study code. The assigned number will correspond to a coded, sealed, pre-packaged bottle containing six doses of either lovastatin or visually matched placebo. Blinding will be maintained amongst the attending physicians and nurses by ensuring that the study drug and the placebo have an identical appearance. In addition the administration schedule will be identical.

### Enrolment

Patients presenting to the out-patients department or in-patient wards with a clinical suspicion of dengue and less than 72 hours of fever will be identified to study staff. Study staff will approach these patients, check eligibility criteria and confirm dengue by NS1 rapid test. Eligible and consenting patients will have screening blood tests sent and provided these are satisfactory will be allotted the next consecutive study number and enrolled to the study.

### Safety reviews

This trial will be conducted in two phases with an escalation of dose if the results of an interim data review show no safety concerns within the first cohort treated with the lower dose. The dose will begin at 40 mg per day in cohort 1 and may continue at 80 mg per day in cohort 2. A DSMB (data and safety monitoring board) review will take place when day 6 study data are available from the 30th patient enrolled in cohort 1. If this review is satisfactory, the dose will be increased to 80 mg per day and recruitment into cohort 2 will commence. Further DSMB reviews will take place when day 6 study data are available from the 30th and 100th patients enrolled in cohort 2.

### Treatment and drug dispensation

Patients will be assigned to one of two treatment arms:

Active medicinal product: 40 mg (stage 1) or 80 mg (stage 2) lovastatin once daily for 5 days.

Placebo: visually matched placebo once daily for 5 days.

The first dose will be given as soon as practically possible after enrolment.

An unblinded study pharmacist will prepare study drug bottles centrally and will distribute the bottles as required. Drugs will be stored in accordance with the manufacturers’ recommendations in a secure area. Lovastatin and the placebo must be maintained below 25°C. All movements of study medication will be recorded. Both individual subject and overall drug accountability records will be kept up to date by the study staff.

